#### Cardiometabolic outcomes

A peripheral intravenous catheter is inserted near the antecubital fossa and a fasting blood sample is taken to measure glucose, serum insulin, HbA1c, high-sensitivity C-reactive protein (hs-CRP), full blood examination (FBE), cholesterol, and triglycerides. Thereafter, the participant is guided through a standard 75-g 2 h OGTT [60], with plasma glucose and serum insulin collected at half-hourly intervals. An additional volume of blood is collected for verification of results if required. Further methodological information is available in Table 4.

**Table 4 Tab4:** Brain health, cardiometabolic biomarkers and more comprehensive methodology descriptions

Cardiometabolic biomarker	Measurement methodology
Glucose	Spectrophotometric-hexokinase method using the Abbott Alinity Analyser
Insulin	Chemiluminescent Microparticle Immunoassay using the Abbott Alinity Analyser
Total cholesterol	Standard enzymatic methods using the Abbott Alinity Analyser
HDL	Accelerator Selective Detergent using the Abbott Alinity Analyser
LDL	LDL will be calculated using the Friedewald formula using the Abbott Alinity Analyser
Hs-CRP	Immunioturbidimetric method using the Abbott Alinity Analyser
HbA1c	Boranate Affinity HPLC method using the Trinity Premier Hb9210.
Full blood examination (FBE)	Beckman Coulter DXH800 instrument
TNF-α, IL-6, IL-1B, adiponectin, and leptin, BDNF,	MAGPIX multiplex microsphere-based immunoassay (Millipore, Billerica, MA)
IGF-1	Human IGF-I/IGF-1 Quantikine ELISA (R&D Systems)
Apolipoprotein E 4 (ApoE-4)	Stored in PAXgene DNA tube, PAXgene Blood DNA kits (QIAGEN) used for DNA isolation, PCR will be performed using custom design primers for the amplification of a segment of the ApoE gene and the 96-well Taqman Gene Expression qPCR Assay (Thermofisher Scientific). ApoE Sequencing (of the PCR product will occur using two single nucleotide polymorphisms (SNPs). Validation of sequencing results will be completed by targeted genotyping via differential amplification of ε2, ε3, or ε3 alleles with custom designed primer pairs.
Serum and plasma analyses	In preparation for serum analyses, samples will be collected in SST tubes and, for plasma analysis, in EDTA tubes. Both samples are rested for thirty minutes in the fridge, prior to centrifuging at 2000 RPM for 15 min at 4 degrees, with the separated plasma and serum aliquoted into 400ul and 750ul volumes and stored at −80 degrees celcius.

#### Inflammatory and neurotrophic factors

Markers of inflammation (e.g. hs-CRP, TNF-α, IL-6, IL-1β, adiponectin, and leptin) and neurotrophic factors (BDNF, IGF-1) will be ascertained from serum/plasma samples collected at all clinical assessments except the 3 month assessment. Samples will be analysed using multiplex microsphere-based immunoassays (MAGPIX, Merck Millipore) and traditional ELISA methods (R&D Quantikine) at the Sunshine Coast Health Institute. Apolipoprotein E 4 (ApoE-4), a commonly assessed genetic risk marker for cognitive decline is assessed at baseline only from DNA isolated from blood collected into PAXgene® tubes using QIAGEN DNA extraction kits. Custom-designed primers will be used for PCR amplification of the ApoE gene (Taqman qPCR,Thermofisher Scientific). Refer to Table 4 for further detail on inflammatory and neurotrophic factor methodologies.

#### Cognitive function

Global cognitive function is first screened with the Addenbrooke Cognitive Examination-Revised (ACE-R) and then assessed using the Cambridge Neuropsychological Test Automated Battery (CANTAB) [61]. The ACE-R is administered by the research staff at baseline only, as it provides a global measure of cognition. ACE-R evaluates six cognitive domains (orientation, attention, memory, verbal fluency, language, and visuospatial ability) and includes an inbuilt Mini Mental State Exam [62].

Following the ACE-R test, CANTAB is completed by the participant at baseline, and then tested additionally at the 6, 12 and 18 month assessments. Specific CANTAB tests (and the domain they measure) are: Paired Associates Learning (visual memory and new learning); Reaction Time (motor and mental response speeds, as well as measures of movement time, reaction time, response accuracy and impulsivity); Delayed Matching to Sample (visual matching ability and short-term visual recognition memory); and, Spatial Working Memory (strategy and working memory). The Motor Screening Task is included as an introduction to the CANTAB assessments. The key primary outcome is the total number of errors on the Paired Associates Learning task adjusted (PAL TEA) shown in Fig. 3. The outcome is automatically calculated by CANTAB. The PAL TEA score represents the number of times a participant chose the incorrect option during the task. Participants that terminate the task early have their scores adjusted; accounting for the estimated number of errors they would have made on all the problems. This allows for comparison with those who completed the final stage of the task. The CANTAB is an iPad administered cognitive battery and results are downloaded from the official Cambridge Cognition platform.

**Fig. 3 Fig3:**
[figure not shown]
Paired Associates Learning task in CANTAB [63]. Participants are shown boxes on the screen containing specific patterns which are “opened” in a randomised order. The patterns are then displayed in the middle of the screen (as pictured) one at a time and the participant must locate which box the designated pattern is in. If the participant makes an error, the boxes are revealed in sequence again and the participant retries the task [64]. Paired Associates Learning task adjusted (PAL TEA) is a primary outcome

#### Anthropometry: height, weight, waist and hip circumferences and body composition

Height is obtained using a stadiometer (Seca, Germany) at the baseline clinic visit only, measured in duplicate, with a third measurement taken if the difference between the first two measurements is ≥0.5 cm. Body mass is measured using a platform scale (JAC-929; Nuweigh, Australia) taking measures in duplicate, with the average of two reading recorded at each assessment. BMI is calculated using height and weight measurements (weight / height^2^). Waist circumference is obtained using a non-elastic tape measure around the midpoint between the iliac crest and the lowest rib. Hip circumference is measured at the maximum circumference in the horizontal plane, over the buttocks. Both measurements are recorded according to the nearest 0.1 cm, and completed twice unless the first two differ by ≥1 cm, in which case a third measure is obtained. A whole-body dual energy x-ray absorptiometry (DXA) scan (Lunar iDXA; GE Healthcare, Australia) is used to assess body composition variables, including total and regional fat mass, and lean mass, and total body fat percentage. Visceral adipose tissue (volume and mass) is estimated by the DXA software using the android region of the body. Where participants’ body size exceeds the DXA scan area, a half body scan is performed, which has previously been shown to provide valid estimate of body composition [65]. Where possible, the same research staff member will perform each participant’s follow-up scan.

#### Blood pressure

Blood pressure is measured via a digital blood pressure monitor (OMRON HEM-907; Omron Healthcare, Japan) placed on the non-dominant arm. Participants are requested to lie down in a dimly lit, temperature controlled (approximately 22–24 C) room. After 10 min of rest, the monitor takes three measurements with an interval of 2 minutes between each measurement. The monitor measures systolic pressure, diastolic pressure, and heart rate and determines the average of the three measurements separately. The three measurements, as well as the average values, are recorded.

#### Arterial function

Arterial function is assessed by flow-mediated dilation (FMD). Participants lie in a supine position in a dimly lit temperature controlled room for at least 20 min before the baseline ‘steady state’ recording of FMD is obtained. Recording is made on the brachial artery of the dominant arm (opposite to blood pressure) using a high-resolution ultrasound machine (Terason t3200, Teratech, Burlington, MA). A rapid inflatable cuff (SC-12-D, D.E. Hokanson Inc., Bellevue, WA) is placed distally to the antecubital fossa and the ultrasound probe applied to the brachial artery. After an optimal image of the brachial artery has been established, a 1 min recording of continuous resting vessel diameter and blood velocity (shear rate) is collected. The cuff is then inflated to > 200 mmHg for 5 min. Thereafter, the cuff is released to induce reactive hyperemia. An additional 3 min of ultrasound recording is completed to determine the post-deflation peak vessel diameter, which is compared to resting vessel diameter (FMD%).

#### Questionnaire measures

Surveys are administered either during the clinic visit, or emailed to the participants for self-completion. All surveys, unless specified otherwise, are combined together into one survey, referred to hereon as the OPTIMISE survey. Contingent on COVID-19 and associated social distancing mandates, all surveys are administered electronically. Information pertaining to questionnaire source, rationale for inclusion, reliability and validity is described below and summarised in Additional file 9.

#### Socio-demographic characteristics

Age and gender are ascertained in the eligibility survey. Sociodemographic characteristics (ethnicity, household type, education, occupation) are obtained at the baseline visit, with question formats based upon previous studies such as the Australian Diabetes, Obesity and Lifestyle (AusDiab) study [66]. Changes in occupation are recorded in follow-up assessments.

#### Health history checklist

A health history checklist recording pre-existing health conditions is recorded by research staff with participants at baseline, and updated throughout the trial in the instance it changes. The checklist includes questions pertaining to any history of angina, heart attack, heart bypass operation, stroke, angioplasty for peripheral vascular disease, kidney damage from diabetes, eye or retinal damage from diabetes, nerve damage from diabetes, numbness burning or tingling in feet, foot ulcer, and lower limb amputation.

#### Self-reported physical activity, sitting time, and sleep

The Active Australia questionnaire is used to measure the number of minutes per week engaged in walking, vigorous gardening, moderate activity, vigorous activity (time multiplied by two), and strength training, with amounts totalled to determine MVPA [67]. The IPAQ questionnaire (two-items) is used to measure overall sitting time obtained in hours and minutes across week days and weekends. Sitting time is contextualised as part of work, travel, recreation, on a screen device, online chores (e.g. emails), or ‘other’ sitting that occurs during waking hours [68]. Sitting time and activity are also assessed using the Sedentary, Transport and Activity Questionnaire (STAQ) [69], which assesses time spent in transport, whether driving, on public transport, walking, and cycling. STAQ has acceptable reliability and validity [69]. Sitting and activity are further quantified using the Occupational Sitting and Physical Activity Questionnaire (OSPAQ) [70]. Here, participants are asked to divide their work day into percentages spent sitting, standing, stepping, and performing heavy labour tasks. OSPAQ has demonstrated acceptable validity and reliability [70, 71]. Additional questions asked include the percentage of the work day that is occupied by prolonged sitting (sitting bouts equal to or greater than 30 min) is also obtained [72], as well as the proportion of the workday spent sitting in common occupational tasks [73]. Participants are asked to identify their desired levels of sitting, standing, and stepping during work and home hours [74]. A 15-item checklist is used to assess participants’ current use of sit less and move more strategies (at home and at work) and a 6-item questionnaire assesses barriers to sitting less and moving more [73]. Knowledge (5-items) and perceived organisational norms (4-items) about sitting, activity, and health are assessed using a questionnaire adapted from a previous trial [75]. Participant’s self-regulation strategies for sitting less and moving more are both assessed with 9-item questionnaires, which are adapted from previous trials [76]. Participants are asked to evaluate how supportive their peers are of reducing sedentary behaviour, as well as engaging in physical activity [77, 78]. Finally, participants are assessed for their perceived changes across 16 domains of sitting in the last 6 months (assessed at 6, 12 and 18 months only). This measure has been adapted from previous research for this trial [79].

#### Sleep diary

Each morning over a 10-day monitoring period (coinciding with the wear of the activity monitor devices), participants are emailed links to a REDCap administered online daily log. Participants can also request to use a handwritten copy of the diary. Using a modified version of the Consensus Sleep Diary [80], the log enquires about their wake (and out of bed) times that morning, their sleep times and sleep quality the night before (into bed, lights out, time to fall asleep, number and duration of awakenings), and over the previous day, their work hours and work location (workplace / home / other), whether each device was worn that day (yes/no) and the start and end times of any removal greater than 10 min. The consensus sleep diary is a validated measure of sleep [81].

#### Anxiety and depression

The Hospital Anxiety and Depression Scale (HADS) [82] is used to measure anxiety and depression. It is a valid and widely accepted measure for determining level of anxiety and depression and can reliably differentiate between the two [83]. The questionnaire consists of 14 items: seven for anxiety (e.g. “I feel tense or wound up”), and seven for depression (e.g. “I feel cheerful”).

#### Managing diabetes

The Problem Areas in Diabetes (PAID) [84] scale assesses perceptions of the intervention and its influence on subjective diabetes management. The measure has demonstrated high reliability [85] and sensitivity to change over time [84], and has demonstrated use for screening depression and emotional problems in people with diabetes [86]. The 5-point scale asks participants to rank aspects of their diabetes management from “Not a problem” to “Serious problem”. Questions pertain to feelings about diabetes treatment and treatment goals, diabetes and social situations, diabetes and adverse events, burden and acceptance of diabetes, and coping with diabetes complications.

#### Fatigue

Fatigue is evaluated with a Fatigue Symptom Inventory (FSI) [87]. The inventory questions the participant on their current and previous level of fatigue in the last week. It examines how their fatigue interferes with activities of daily living, cognition, relationships, and mood. Participants are asked to rate the level of fatigue on a 0 (no fatigue) to 10 (extreme fatigue) scale. The measure has demonstrated validity with other fatigue symptom measures [87, 88].

#### Musculoskeletal pain and health

Musculoskeletal pain and health is measured using the 27-item modified Nordic Musculoskeletal Questionnaire, which surveys both the last 3 months and the last 7 days [89]. Participants indicate the body locations they have experienced ‘trouble’ in muscles or joints. Pain is ranked with an adapted 0–10 scale [90], where 0 indicates ‘no pain’, and 10 indicates the ‘worst pain imaginable’. This measure has been demonstrated to be repeatable and sensitive to change [91].

#### Work

Participants are asked to estimate their hours and days working, and how many leave days they have had in the preceding 3 months due to illness. Perceived workload and caring responsibility are assessed with a valid [92] two-item questionnaire based on the Borg workload scale [93], and NASA Task Load Index [94]. Self-reported work satisfaction [95] and work performance [96] are also assessed via 7-point scales. Participants are surveyed for how they feel during work with the ultra-short measure for work engagement (UWES-3) [97] featuring 3-items with a 7 point scale, including energy levels, enthusiasm, and being immersed in their work. The Work Limitations Questionnaire (WLQ) [98] is used to examine the frequency of difficulty that the participant has with performing specific work-related tasks. The WLQ has demonstated validity and reliability and is correlated with arthritis pain, as well as functional limitations and work productivity [98].

#### Workplace environment

An audit of the participant’s work environment is conducted at baseline only and made according to the Checklist of Health Promotion and Environments at Worksites (CHEW) [99] which was successfully modified for sedentary behaviour interventions in BeUpstanding [100]. Information is captured on layout, the nearby physical environment (e.g. stairs, centrally located printers and amenities), and workplace policy (such as flexible work hours). The 26-item questionnaire also includes questions pertaining to whether the workplace provides sit-stand desks, and whether a wearable tracker has been previously provided by employers.

#### Medication and allied health appointments

A record of the participant’s medication, including dosage, frequency is created at the baseline clinical assessment. Any changes to their medication is noted at each subsequent assessment. Similarly, any appointments with an allied health professional in the preceding months between clinical visits are recorded and updated at each assessment. Both records inform potential confounding effects of medication and allied health treatment on the primary and secondary analyses.

#### Personal wearables questionnaire

Participants use of wearable activity trackers and/or apps in the preceding months is recorded at each visit. Questions about type of wearable and app have been adapted from previous research [101], with the inclusion of additional questions pertaining to how long they have been using the device for, what feature they use (e.g., step counts, exercise intensity), how often they follow associated prompts, and whether these are followed at work, home, or both. Similar questions have been used in previous workplace sedentary behaviour interventions [101] and are important for evaluating prior exposure to health-behaviour trackers.

#### Dietary intake

Dietary intake is measured using the University of Newcastle’s Australian Eating Survey (AES), a Food Frequency Questionnaire which examines eating habits over the previous 3–6 months [102]. It is a semi-quantitative questionnaire of 120 items. The questionnaire has comprehensive validaty and reliability [103], requires less time to complete compared to a 24-h dietary recall, and is representative of longer term changes in dietary intake. Completion of the questionnaire results in a report detailing total daily energy intake, the contribution of healthy nutrient-rich and unhealthy nutrient-poor food choice to diet, the Australian Recommended Food Score (ARFS) a diet quality score indicative of the participant’s alignment to Australian dietary recommendations, macronutrient intake, micronutrient intake and fibre intake. The results are considered as confounding variables on primary and secondary analyses.

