### Data collection

Data collection occurs at baseline, 3, 6, 12, 15 and 18 months via: in-person clinical assessments; cognitive testing; device-based monitoring; and online questionnaires administered through REDCap; and, process data collected in REDCap and by the health coach in REDCap health-coaching forms. Table 2 shows the timepoints at which each component of the data-collection occurs under the original, expanded, and COVID-adapted protocols. Table 3 and Additional file 9 provide extensive details of the objective and questionnaire measures, as well as their intended purpose in the trial (e.g., primary outcome, secondary outcome, process outcome). The data collection procedures used for each of these components are indicated below.

**Table 2 Tab2:** Data collection components and timepoint of collection

Data collection component		Timepoint					
		0 M	3 M	6 M	12 M*	15 M*	18 M*
Clinical assessment (in person)	Fasting venous blood draw ^a^	✓	✓	✓	✓		✓
	OGTT ^b^	✓	✓	✓	✓		✓
	Anthropometric ^b^	✓	✓	✓	✓		✓
	DXA ^b^	✓	✓	✓	✓		✓
	Blood Pressure ^b^	✓	✓	✓	✓		✓
	FMD ^b^	✓	✓	✓	✓		✓
	Cognitive Testing ^b^	✓		✓	✓		✓
Device-based monitoring	activPAL	✓	✓	✓	✓	✓	✓
	GT3X+	✓	✓	✓	✓		✓
	Activity Monitor Diary	✓	✓	✓	✓	✓	✓
Surveys (administered during clinic visit)	Health History Survey	✓					
	Medication Log ^a^	✓	✓	✓	✓		✓
	Allied Health Log ^a c^	✓	✓	✓	✓		✓
	OPTIMISE Survey ^a^	✓	✓	✓	✓	✓	✓
	Personal wearables questionnaire ^b c^	✓	✓	✓	✓		✓
	‘Typical 24 h’ Survey ^d^	✓	✓				
Surveys (self-completion)	Dietary intake questionnaire	✓	✓	✓	✓		✓
	Quality of Life Survey	✓	✓	✓	✓		✓
	Menstrual Status Questionnaire ^c^ (women only)	✓		✓	✓		✓
	Motivation for Physical Activity Survey ^c^	✓	✓	✓	✓		✓
	Motivation to Break Up Sitting survey ^c^	✓	✓	✓	✓		✓
	OPTIMISED Survey (delayed intervention) *					✓	✓
	COVID-19 impact questionnaire ^e^	✓		✓	✓	✓	✓
Implementation / intervention fidelity data	REDCap Metadata: instrument status, dates & times	✓	✓	✓	✓	✓	✓
	Fitbit usage		✓	✓	✓	✓	✓
	propelo™ message log: full record of all messages sent/received			✓	✓	✓	
	Health coaching forms		✓	✓			
	Tailoring forms			✓			
	Withdrawal and adverse events log ^f^	✓	✓	✓	✓	✓	✓

Abbreviations: *OGTT* oral glucose tolerance test, *DXA* dual energy x-ray absorptiometry; *FMD* flow-mediated dilation

* Expanded protocol only

^a^ Replaced with COVID-safe alternative during restrictions (self-completion questionnaire; self-report; no clinical visit, pathology visit HbA1c test only)

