#### Statistical analyses

Outcomes are all continuous and expected to be either normal or log-normal, in which case log-transformation will be used. Analyses will be performed in STATA version 15 or higher. Significance is set at *p* < 0.05 two-tailed (except for *p* < 0.025 when testing co-primary outcomes based on α = 0.025). To test the differences between groups in primary and secondary outcomes during (3 months), end of the intervention (OPTIMISE; 6 months) and end of the extended maintenance phase (12 months – OPTIMISE-extended) mixed models statistical analysis will be employed, accounting for repeated measures, adjusting for baseline values, randomisation strata, and potential confounders. Within-group changes for intervention participants occurring during the no health coaching contact phase from 12 to 18 months will be tested and compared to intervention phases. Within-group changes will also be tested in the delayed intervention participants receiving the OPTIMISED intervention after 12 months, at the 18 month timepoint, using paired t-tests (or non-parametric paired tests). Possible confounders will be identified a priori from the literature and narrowed down to a number that can be modelled without overfitting, based on an objective criterion not open to manipulation (backwards elimination: retaining age, sex, and *p* < 0.2 association with the outcome). Analyses will follow intention-to-treat principles. Sensitivity to handling missing data will be evaluated by comparing results from the main analyses (evaluable case analysis for mixed models; complete-case analysis for t-tests) with alternative methods that are appropriate for different missing data scenarios (e.g., multiple imputation; selection-covariate adjustment). Descriptive statistics will be used to describe the implementation indicators of the different phases of the intervention.

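### The protocol permits diet, medication and allied-health data recorded after randomisation to be adjusted for as confounders in the main between-group models

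*Protocol article*

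**What the plan says.** Three places in the Methods of the protocol article bear on this.

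- **Dietary intake.** Of the food-frequency questionnaire: "The results are considered as confounding variables on primary and secondary analyses". No time point is attached. The instrument is chosen partly because it "is representative of longer term changes in dietary intake", and Table 2 (Data collection) schedules it at 0, 3, 6, 12 and 18 months.
- **Medication and allied health appointments.** "Any changes to their medication is noted at each subsequent assessment", and "any appointments with an allied health professional in the preceding months between clinical visits are recorded and updated at each assessment". Then: "Both records inform potential confounding effects of medication and allied health treatment on the primary and secondary analyses".
- **Statistical analyses.** The mixed model for the 3-, 6- and 12-month comparisons is fitted "adjusting for baseline values, randomisation strata, and potential confounders". On selection: "Possible confounders will be identified a priori from the literature and narrowed down to a number that can be modelled without overfitting". The narrowing is by backwards elimination, which keeps age, sex and anything associated with the outcome at p < 0.2. The same section says the analyses follow intention-to-treat principles.

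Study design and randomisation places allocation at the end of the baseline assessment. Every follow-up entry in these records is therefore post-randomisation.

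**The concern.** Randomisation makes the arms comparable on everything that precedes it. A variable measured afterwards cannot confound the comparison, but it can be a consequence of allocation. Diet may shift with engagement in either arm, glucose-lowering medication may be changed in response to HbA1c, and use of other services may differ because participants know their arm. Conditioning on such a variable removes whatever part of the effect runs through it. Where the variable shares an unmeasured cause with the outcome, conditioning also opens a non-causal path between arm and outcome. The coefficient for arm is then not the intention-to-treat effect that the Statistical analyses section promises.

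The selection rule gives no protection. It asks whether a candidate predicts the outcome, not when it was measured. Follow-up diet and medication plausibly predict HbA1c, so a p < 0.2 rule would tend to keep them.

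**Working it through.** **1. Do the passages, read together, allow follow-up values into the model?**

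- Dietary intake names the questionnaire results as confounders. Four of the five scheduled measurements come after randomisation.
- The medication and allied-health section refers to both records, and its description of those records expressly includes later changes and appointments between visits.
- The Statistical analyses section lists baseline values and potential confounders as separate items and restricts only the first to baseline.
- Baseline medication count (0–1 or 2+ agents) is already in the model as the randomisation stratum, so much of what the running log could add is follow-up information.

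The answer is that the text allows it but does not require it.

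**2. The plan's own sample size.** Inputs from Sample size: two-sided α = 0.025, power 0.80, attrition 20%; HbA1c difference 0.5, SD 1.6, r 0.7; sitting difference 0.5, SD 1.3, r 0.6.

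- Baseline-adjusted SD: s = SD·√(1 − r²). HbA1c: 1.6·√0.51 = 1.143. Sitting: 1.3·√0.64 = 1.04.
- n per arm = 2(z₀.₉₈₇₅ + z₀.₈₀)²·s²/d². HbA1c: 100, and 100/0.80 = 125. Sitting: 83, and 83/0.80 = 104 after rounding up.

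The stated 125 per arm is reproduced exactly, with adjustment for the baseline outcome alone. Power at 100 evaluable per arm is 0.803 for HbA1c and 0.877 for sitting. Restricting the other covariates to baseline changes none of this.

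**3. What adjustment could do (assumed inputs).** The documents give no effect of allocation on diet, medication or allied-health use, so only a range can be shown. Suppose a share of the 0.5 difference runs through the adjusted covariate. The adjusted effect is then 0.5·(1 − share), and power = Φ(d/(s·√(2/100)) − 2.241), with s held fixed.

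| Share | Adjusted effect | Power, HbA1c | Power, sitting |
|---|---|---|---|
| −20% | 0.60 | 0.929 | 0.967 |
| 0% | 0.50 | 0.803 | 0.877 |
| 10% | 0.45 | 0.707 | 0.793 |
| 20% | 0.40 | 0.592 | 0.684 |
| 30% | 0.35 | 0.470 | 0.555 |
| 50% | 0.25 | 0.244 | 0.294 |

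A negative share means that the path through the covariate opposes the intervention effect.

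**4. Mediator and collider together.** Let τ be the total effect, a the shift in a unit-variance covariate due to arm, b its effect on the outcome, and g and u the effects of an unmeasured common cause on covariate and outcome. The adjusted coefficient is τ − a(b + gu). With τ = −0.50 and a = −0.3:

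- b = 0.3, no common cause: −0.50 + 0.09 = −0.41
- b = 0.5, no common cause: −0.50 + 0.15 = −0.35
- b = 0.3, g = u = 0.5: −0.50 + 0.3·(0.3 + 0.25) = −0.335
- b = 0, g = u = 0.5: −0.50 + 0.3·0.25 = −0.425, biased although the covariate has no effect on the outcome

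With a = 0 the result is −0.50, with no bias. With a = +0.3 and b = 0.3 it is −0.59, away from zero. A simulation of 400,000 records agreed with the four listed cases and the a = 0 case to within 0.01. For medication even the sign of (b + gu) is uncertain: treatment lowers HbA1c (b negative), while poor control prompts treatment (gu positive).

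**The case against.** The strongest reply is that the article never says follow-up values enter the primary model. The diet sentence gives no time point, and the medication sentence says only that the records inform potential confounding. That wording also fits a descriptive check, a sensitivity analysis or baseline adjustment. All three variables are at most candidates subject to elimination, the intention-to-treat statement favours a baseline reading, and the final covariate list may sit in a statistical analysis plan that is not shown.

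Much of this stands. A reader might infer that the plan commits to adjusting for follow-up diet and medication, and so shrinks the intervention effect. The documents support neither half of that. No sentence makes the commitment. As for direction, the coaching described concerns sitting less and moving more and has no dietary content. Controls receive monthly diabetes-management fact sheets with follow-up calls, and both arms may seek other lifestyle interventions. A dietary shift could favour either arm.

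The appeal to an unseen analysis plan does not dispose of the point. The article does not merely leave the timing open. It names repeatedly updated records as confounders of the primary analyses and supplies a selection rule that ignores timing. An analyst following these passages as written could put post-randomisation variables into the main model and be within the protocol.

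**Conclusion.** The point holds as a permission, not as a stated intention. As written, the protocol allows post-randomisation diet, medication and allied-health data into the main between-group models, contrary to its own intention-to-treat principle. Bias follows only if the arms differ on those variables. It can go in either direction, and the documents do not allow its size to be computed. The 0.40 and 0.60 figures for 20% shares in either direction, and the −0.335 to −0.59 range of adjusted coefficients, illustrate assumed inputs and are not estimates for this trial. The power figures cover HbA1c and sitting time; the cognitive outcome was not worked, though the same reasoning applies to it. The sample size of 125 per arm is unaffected.

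**What to change.** State in Dietary intake, in Medication and allied health appointments, and in Statistical analyses that covariates in the primary and secondary between-group models are restricted to values measured before randomisation: baseline outcome, stratum, age, sex, baseline medication, baseline diet and baseline allied-health use. Report follow-up changes in diet, medication and allied-health use by arm, and use them only in analyses labelled as mediation or sensitivity analyses.

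The cost is a few sentences, with no new data and no change to the sample size. One practical limit is that Table 2 marks the allied-health log as added part way through the study. Its baseline value may be missing for early participants, so the text should say how that is handled or leave it out of the candidate list. The change should be made before outcomes are analysed by arm, because a covariate choice that moves a primary estimate is hard to defend afterwards.
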